### Statistical analysis

#### Primary analysis

To compare the effectiveness of the three feedback strategies in improving the FI score, we will use *mixed-effects regression models*: multiple, linear, multi-level regression models including random and fixed (or mixed) effects.

#### Controlling for potential biases

We will account for multiple measures within each unit and clustering of units within facilities. We will adjust all analyses for the three stratification variables of the TREC facility sample (region, owner-operator model and facility size). We will compare characteristics of units and facilities using descriptive statistics at baseline, and adjust where there are significant differences between treatment groups (as baseline difference can occur by chance despite appropriate randomization). Should data not meet the assumptions of this model (multivariate normality, linearity, normally distributed, uncorrelated residuals, random effects with mean zero) the model will be adjusted accordingly. Within TREC, there is an extensive program to monitor and assure data quality, and a comprehensive data cleaning processes [123]. We will carry out an intention-to-treat analysis, as this best reflects the pragmatic nature of the study. We will compare these results to a per-protocol analysis, which better reflects adherence/non-adherence with the intervention. We will consider a care unit to be adherent with the intervention if at least one representative of this unit attends the Goal Setting Workshop and at least one of the two Support Workshops. The person attending the Goal Setting Workshop can be different from the person attending the Support Workshop(s). Units only attending the Goal Setting Workshop or not attending any of the workshops will be defined as non-adherent. We have registered the trial with ClinicalTrials.gov (NCT02695836) and we will use CONSORT guidelines [124] to report its findings.

#### Secondary analyses

We will monitor change of secondary outcomes over time in each study arm, and compare outcomes between three study arms using descriptive statistics, statistical process control methods and appropriate significance tests (t tests for normally distributed, linear, continuous outcomes; non-parametric tests for variables that do not meet these assumptions; chi-squared tests for categorical outcomes). We will longitudinally track two practice sensitive RAI QIs (worsening pain, declining behavioural symptoms), using statistical process control methods [125–128]. We will calculate risk-adjusted and unadjusted indicators and, using control charts, graphically display unit and facility performances. These data will enable us to assess possible effects of *INFORM* on resident care as measured by resident QIs at a time consistent with the intervention. We will assign a dichotomous variable (*improved/not improved*) to each unit in the intervention. Then, using logistic regression with *improvement* as the outcome we will investigate the effects of context (using ACT scales), best practice use, and staff characteristics on improvement. To this end we have developed a reliable classification system for individual control charts [49, 50].

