**Methods:**

INFORM (Improving Nursing Home Care through Feedback On PerfoRMance Data) is a 3.5-year pragmatic, three-arm, parallel, cluster-randomized trial. We will randomize 67 Western Canadian nursing homes with 203 care units to the three study arms, a standard feedback strategy and two assisted and goal-directed feedback strategies. Interventions will target care unit managerial teams. They are based on theory and evidence related to audit and feedback, goal setting, complex adaptive systems, and empirical work on feeding back research results. The primary outcome is the increased number of formal interactions (e.g., resident rounds or family conferences) involving care aides – non-registered caregivers providing up to 80% of direct care. Secondary outcomes are a) other modifiable features of care unit context (improved feedback, social capital, slack time) b) care aides’ quality of worklife (improved psychological empowerment, job satisfaction), c) more use of best practices, and d) resident outcomes based on the Resident Assessment Instrument – Minimum Data Set 2.0. Outcomes will be assessed at baseline, immediately after the 12-month intervention period, and 18 months post intervention.

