## Methods/Design

### Design

This is a protocol for a pragmatic, three-arm, parallel, cluster-randomized trial using stratified permuted block randomization with baseline assessment, a one-year intervention period, post-intervention assessment, and 18-months long-term follow-up (Table 1). This protocol followed the SPIRIT reporting guidelines for trial protocols [107] (Additional file 1). Should we need to make important modifications to this protocol, we will revise our study registration and ethics application (including all relevant study documents) accordingly, inform all relevant stakeholders (investigators, trial participants, regulators), and will report protocol changes in our final publication of study results. We have established a structure of committees and working groups to facilitate intervention development and implementation, and to ensure scientific rigor (Additional file 2). We will disseminate study results in peer-reviewed publications and international conference presentations.

**Table 1 Tab1:** Schedule of enrolment, interventions, and assessments (adapted SPIRIT flow diagram [107])

	T_-2_ (09/14-04/15)	T_-1_ (10/15-11/15)	T_0_ (11/15-05/16)	T_1_ (05/16-06/16)	T_1_ (10/16-11/16)	T_1_ (04/17-05/17)	T_x_ (05/17-12/17)	T_x_ (01/19-06/19)
	Baseline	Dissemination workshop	Study preparation	Goal setting workshop	Support workshop 1	Support workshop 2	Post intervention	Long-term follow-up
Assessment of primary and secondary study outcomes *(all facilities participating in TREC)*								
TREC survey	X						X	X
RAI-MDS 2.0	X						X	X
Unit profile survey	X						X	X
Facility profile survey	X						X	X
Enrolment *(all TREC facilities in Alberta and British Columbia)*								
Ethics/operational approvals			X					
Eligibility screening			X					
Randomization/allocation			X					
Recruitment and informed consent *(BAF/EAF)*			X					
Study intervention								
Standard Feedback *(SF)*		X						
Basic Assisted Feedback *(BAF)*		X		X	X (virtual)	X (virtual)		
Enhanced Assisted Feedback *(EAF)*		X		X	X (face-to-face)	X (face-to-face)		
Ongoing phone/e-mail support *(EAF)*				–––––––	–––––––	–––––––		
Process evaluation								
Workshop evaluation surveys (at the end of each workshop)		X		X	X	X		
Workshop fidelity checklist and debriefs (at the end of each workshop)		X		X	X	X		
Detailed documentation of workshops (participant observations)					X (during workshops)			
Focus groups with *BAF/EAF* unit managers						X (05/2017)		X (12/2018)

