### Outcomes and instruments

Additional file 7 contains a summary table listing study outcomes, tools used to assess these outcomes, and their psychometric properties. Our outcome definition includes the name of the outcome, the time point each outcome will be assessed, the method of aggregation, the metric (e.g., change from baseline or group differences at a given time), the definition of the concept assessed, psychometric properties and an example item of each scale used.

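### The simple tests named for the secondary between-arm comparisons use the collected baseline values at best as change scores and cannot carry the covariate adjustment promised elsewhere; conditioning on baseline would gain precision at no data cost

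*Protocol article*

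**What the plan says.** The Abstract (Methods) schedules three assessments: "Outcomes will be assessed at baseline, immediately after the 12-month intervention period, and 18 months post intervention". Table 1 marks the care aide survey, the resident assessment data and the unit and facility profile surveys at baseline, post-intervention and long-term follow-up for all TREC facilities. The survey-based secondary outcomes therefore all have a baseline value.

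Secondary analyses sets out the arm comparison: "We will monitor change of secondary outcomes over time in each study arm, and compare outcomes between three study arms using descriptive statistics". The section then adds methods of statistical process control and names the tests of significance: "t tests for normally distributed, linear, continuous outcomes; non-parametric tests for variables that do not meet these assumptions; chi-squared tests for categorical outcomes". The logistic regression later in that section relates unit improvement to context, best practice use and staff characteristics. It does not compare arms.

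Controlling for potential biases promises, for all analyses, adjustment for region, owner-operator model and facility size. It also promises to account for repeated measures and for clustering of units in facilities. On baseline differences in unit and facility characteristics it says to "adjust where there are significant differences between treatment groups".

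Outcomes and instruments refers to Additional file 7 (not shown) for each outcome's definition, including "the metric (e.g., change from baseline or group differences at a given time". Whether the tests would be applied to follow-up values or to change scores is therefore open.

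**The concern.** A t test, a rank test or a chi-squared test has no place for a covariate. Applied to follow-up values, it ignores baseline. Applied to change scores, it uses baseline with a fixed coefficient of 1, which over-corrects whenever the wave-to-wave correlation is below 1. Neither version can deliver the covariate adjustment promised for all analyses, so the two sections do not fit together. A cluster-correct version, for example a t test on facility means, would leave the baseline problem as it is.

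This matters because the Discussion expects the two assisted feedback arms to be significantly more effective than standard feedback on context overall and on care provider outcomes, not only on FI. With 67 facilities in three arms (about 22 per arm), chance baseline differences can be material, and an inefficient comparison is more likely to miss a modest real effect.

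**Working it through.** **Inputs.** From Sample size calculation: SD of the facility effect 0.154, of the unit effect 0.104 and of the residual 0.192, with 3 units per facility. These describe FI; the article gives no such figures for any secondary outcome, so they serve only as an illustration. Assumed increases are 0.2, 0.4 and 0.6, so adjacent arms differ by 0.2. Two-sided alpha of 0.05 is my assumption, because the article states none.

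**Correlation between two waves.**
- Squared SDs: 0.0237, 0.0108 and 0.0369.
- Units: (0.0237 + 0.0108) / (0.0237 + 0.0108 + 0.0369) = 0.484.
- Facility means of 3 units: variance V = 0.0237 + 0.0108/3 + 0.0369/3 = 0.0396; correlation = (0.0237 + 0.0108/3) / 0.0396 = 0.690.

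**The plan's own figure.** The article states power 0.90 with 12 facilities per arm for FI. With facility means, one follow-up wave and an adjacent-arm difference of 0.2:
- baseline as covariate: variance 0.0396 × (1 − 0.690²) = 0.0208; power 0.909 (noncentral t), 0.904 (simulation, 8,000 runs);
- change score: 0.858;
- follow-up only: 0.666.

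Of these three, the baseline-adjusted analysis matches the stated 0.90. This fits the article's FI model, which has a common mean, exposure indicators, and facility and unit effects shared over time, so that baseline informs the effect estimate. The match is not proof of what was simulated: the contrast and alpha are not stated, and adding a second follow-up wave gives 0.982.

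**Relative variance of the three analyses** (follow-up only = 1; change score = 2(1 − r); baseline-adjusted = 1 − r²):

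| | r | Follow-up only | Change score | Baseline-adjusted |
|---|---|---|---|---|
| Units | 0.484 | 1 | 1.03 | 0.77 |
| Facility means | 0.690 | 1 | 0.62 | 0.52 |

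- Saving against follow-up only is r²: 23% for units, 48% for facility means.
- Saving against a change score is (1 − r)/2: 26% for units, 15.5% for facility means.
- Assumed r of 0.3, 0.5 and 0.7: 9%, 25% and 49% against follow-up only; 35%, 25% and 15% against a change score.

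In facilities per arm for power 0.90 at a difference of 0.2 (normal approximation), facility means need 21 (follow-up only), 13 (change score) or 11 (baseline-adjusted).

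**The significance trigger.** With 22 facilities per arm, the difference in baseline means between two arms has standard error √(2/22) = 0.30 facility-mean SD. An imbalance up to about 1.96 × 0.30 = 0.59 SD is non-significant and would not trigger adjustment. At r = 0.69 about 0.69 × 0.59 = 0.41 SD of it is expected to carry into a follow-up-only comparison.

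**The case against.** Several points on the other side are sound and limit what can be claimed.

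- **Baseline may be used.** A reader might infer that baseline plays no part in the arm comparison. The documents do not support that: Secondary analyses begins with monitoring change, and change from baseline is one of the metrics named under Outcomes and instruments. If change scores on facility means are used, they already secure 38 of the 48 percentage points, about four fifths. On unit values they gain nothing (relative variance 1.03).
- **Imbalance is not wholly ignored.** A reader might infer that chance imbalance goes uncorrected. The significance-triggered rule is a stated correction. It is weak, it refers to unit and facility characteristics rather than clearly to each outcome's own baseline, and the named tests cannot carry it out.
- **No bias.** Under randomization, follow-up-only and change-score comparisons are both unbiased.
- **Resident outcomes.** The two resident quality indicators are tracked longitudinally by control charts in risk-adjusted and unadjusted form, so earlier values are used there. The point is confined to survey-based outcomes.
- **Borrowed correlations.** By Table 1, baseline precedes post-intervention by about 25 to 39 months and long-term follow-up by about 45 to 57 months. If correlation fades over such gaps, the savings against follow-up only move toward the low end. The formula also does not carry over directly to categorical outcomes.
- **Spare sample size.** At 22 facilities per arm and an FI difference of 0.2, power is 0.91, 0.99 and 0.995 for follow-up only, change score and baseline adjustment. This comfort goes with the effect size. For an assumed difference of 0.1, the standard errors √(2 × variance/22) are 0.060, 0.047 and 0.043, and normal-approximation power is about 0.38, 0.56 and 0.63.
- **Left to the analysis plan.** Covariates for secondary outcomes often are. Here, however, the article names specific tests that conflict with its own promise for all analyses, so an analysis plan would have to override this text rather than complete it.

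**Conclusion.** The point holds as a matter of efficiency and internal consistency for the survey-based secondary outcomes. The named tests use the baseline at most as a change score and cannot carry the adjustment promised under Controlling for potential biases.

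On the FI components, conditioning on baseline would remove about 23% (units) to 48% (facility means) of the variance of a continuous outcome relative to a follow-up-only test. Relative to a change score it would remove about 26% to 15.5%. The first pair are shares of the outcome variance. A reader might take them as the part of the obtainable gain that is lost, but a follow-up-only test forgoes all of that gain.

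The sizes assume that the secondary outcomes behave like FI and that correlation does not decay over the gap between waves. The range of 9% to 49% against follow-up only, for correlations of 0.3 to 0.7, is the safer summary. The validity of the trial is not in question. The change is worth making because it is free and because effectiveness is hypothesized on these outcomes.

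**What to change.** In Secondary analyses, replace the list of tests as the basis for between-arm inference. Compare arms on each survey-based secondary outcome with a mixed model (generalized for categorical outcomes) that:

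- accounts for clustering of units in facilities, and carries the adjustment for region, owner-operator model and size already promised;
- always includes the outcome's own baseline value at the level of analysis (unit or facility), either as a prespecified covariate or as the first repeated measure with a common baseline mean, as the FI model in Sample size calculation does;
- does so whatever the baseline significance tests show.

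Keep the t, non-parametric and chi-squared tests for description only. The control-chart tracking of the resident indicators can stay as it is.

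The cost is a change of wording and a little more analysis work. No new data are needed, because the baseline values come from the TREC survey wave already scheduled for every facility.

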### Sample

#### Sample size calculation

The intervention target are the nursing home care units (clinical microsystems). To avoid contamination effects, we will randomize at the facility level, with all unit managers of the same facility receiving the same feedback intervention. Due to the three-arm design, multiple repeated measures, and the complex nested structure (time points nested within each care unit, and units clustered within facilities), basic methods of sample size estimation are not applicable [108–110]. Therefore, we adapted a computer simulation-based approach described by Arnold et al. [108] using the statistics software R (version 3.1.2) [111]. Power and sample size were based on the following mixed-effects regression model:$$ {Y}_{ijt}=\mu +{\beta}_1\;A{1}_{ijt}+{\beta}_2\;A{2}_{ijt}+{\beta}_3\;A{3}_{ijt}+{b}_i+{b_i}_j+{\varepsilon}_{ijt} $$
Y_ijt_ is the ACT *Formal Interactions* (FI) score (primary outcome) of unit j in facility i at time t.μ is the FI population mean.A1_ijt_, A2_ijt_, and A3_ijt_ are indicator variables for the interventions (SF, BAF, and EAF, respectively). The indicator variable is 1 if the unit has been exposed to the respective intervention and 0 otherwise.β_1_, β_2_, and β_3_ are the treatment effects of the three interventions.b_i_ is a facility-level random effect (variability of units within the facility).b_ij_ is a unit-level random effect (variability of time points within the unit).ε_ijt_ is a residual term (variability between units).

We assumed that the random effects and the residual term were normally distributed with mean zero and uncorrelated with one another. Using data from the previous phase of TREC (2007–2012) we estimated the following parameters to be entered into the model:μ = 1.1 (FI mean was 1.32. Standard feedback here is similar to that provided in the previous TREC phase [112–114]. We assumed that this intervention will, at least, have a small effect (increase the FI score by 0.2) compared to no feedback.Standard deviation of b_i_ = 0.154 (ICC = 0.445) (FI variability of units, within facilities)Standard deviation of b_ij_ = 0.104 (FI variability of units, across waves 1 and 2 in TREC 1.0)Standard deviation of ε_ijt_ = 0.192 (variability of the unit FI residual term)Average cluster size = 3 units per facility

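### The between-arm tests named for secondary outcomes take account of neither facility randomisation nor the covariate adjustment promised for all analyses; a nominal 5% unit-level test could run at about 13% if the outcome clusters like FI

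*Protocol article*

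**What the plan says.** All references are to the protocol article.

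- **Unit of randomisation** (Sample size calculation): "we will randomize at the facility level, with all unit managers of the same facility receiving the same feedback intervention".
- **Primary analysis:** a multilevel mixed-effects regression is named, for the FI score only.
- **Clustering** (Controlling for potential biases): "We will account for multiple measures within each unit and clustering of units within facilities".
- **Covariates** (same section): "We will adjust all analyses for the three stratification variables of the TREC facility sample". These are region, owner-operator model and facility size.
- **Secondary analyses:** change is to be monitored over time in each arm. The three arms are then compared by descriptive statistics, by statistical process control, and also by "appropriate significance tests (t tests for normally distributed, linear, continuous outcomes; non-parametric tests for variables that do not meet these assumptions; chi-squared tests" (the last of these applies to categorical data). The section mentions no clustering correction, facility-level aggregation or covariate adjustment for these tests.
- **Planning values, FI only** (Sample size calculation): "Standard deviation of b_i_ = 0.154 (ICC = 0.445"), "Standard deviation of b_ij_ = 0.104", "Standard deviation of ε_ijt_ = 0.192" and "Average cluster size = 3 units per facility". The article gives no ICC for any secondary outcome and no alpha for the secondary tests.

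**The concern.** Ordinary t, rank and chi-squared tests treat every observation as independent. Units in one facility share an allocation and, on the plan's own FI figures, resemble each other. Treating them as independent makes the standard error of an arm difference too small and the test too liberal. These tests also have no place for the three stratification covariates.

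This goes beyond detail that an article leaves to a fuller plan, because the article names the tests. If the commitments under Controlling for potential biases govern, the named tests are the wrong ones. If the named tests govern, the commitments are not met.

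The Discussion hypothesises that both assisted strategies will be significantly better than standard feedback on context, care-provider and resident outcomes. The listed tests are the significance tests the article names for comparing those outcomes between arms. At stake is an excess of false-positive secondary findings.

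**Working it through.** **Do the planning values behave as understood?** Take the FI model with its three SDs, 3 units per facility, baseline plus one post-intervention measure and two-sided 5% (assumed). Twelve facilities per arm then give 92.5% power for a 0.2 difference between adjacent arms, and 11 give 90.2%. The plan states 12 for 0.90, so its SDs can be used as they stand. It states no type I error for the secondary tests, so there is no such figure to reproduce.

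**ICC from the stated SDs.** The correlation between two units of one facility at one time is

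ICC = 0.154² / (0.154² + 0.104² + 0.192²) = 0.023716 / 0.071396 = 0.332.

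The printed 0.445 is not this variance ratio. It equals a ratio of SDs, 0.154 / (0.154 + 0.192) = 0.445. Both are carried below, and 0.332 is the better supported.

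**Cluster size.** The plan gives 3 units per facility; 203 / 67 = 3.03 agrees.

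**True size of a unit-level t test on post-intervention values.** Design effect DE = 1 + (m − 1) × ICC with m = 3. True size = 2 × [1 − Φ(1.96 / √DE)].

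| ICC | Source | DE | True size |
|---|---|---|---|
| 0.01 | assumed | 1.02 | 5.2% |
| 0.05 | assumed | 1.10 | 6.2% |
| 0.10 | assumed | 1.20 | 7.4% |
| 0.20 | assumed | 1.40 | 9.8% |
| 0.332 | FI, from stated SDs | 1.664 | 12.9% |
| 0.445 | FI, as printed | 1.890 | 15.4% |

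**Simulation check** (no true effect, two arms of 22 facilities with 3 units each):

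| Test | ICC 0.332 | ICC 0.445 |
|---|---|---|
| t test on units | 13.1% | 15.8% |
| Mann-Whitney on units | 13.4% | 15.1% |
| Chi-squared on units, outcome split at the median | 9.8% | 11.1% |
| t test on facility means | 4.9% | 5.1% |

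The last row shows that the excess comes from clustering and disappears when the facility is the unit of analysis.

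**Change scores.** In the plan's model the facility and unit effects do not vary with time, so both cancel in post minus baseline. Only the residuals remain, and they are independent between units. The simulated size of a t test on change is 4.9%.

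**One value per facility.** With m = 1, DE = 1 and there is no inflation from this source. Performance reports and quality improvement activities come from the facility survey (Secondary outcomes, Organizational), so analysed per facility they fall here.

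**The case against.** The strongest reply is that Secondary analyses is silent on clustering rather than opposed to it. The commitments in the preceding section could be read as governing it, and a t test on facility means would respect the randomisation. That stands in part: it is an inference that the tests would be run on units as if independent. It does not reconcile the text, because the covariate commitment covers all analyses and an unadjusted t, rank or chi-squared test cannot meet it at any level of aggregation.

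Several stronger readings are tempting, but the documents do not support them.

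- *All secondary tests run at 13-15%.* That range borrows the ICC of the primary outcome and assumes unit-level post-intervention values. Its upper end relies on a printed ICC that the stated SDs do not give. Slack time, evaluation and social capital come from the same instrument as FI, so borrowing is reasonable there as a labelled assumption. It remains an assumption.
- *Every secondary outcome is affected.* Facility-survey outcomes have no units nested within them.
- *Baseline is not used.* Outcomes and instruments says that Additional file 7 sets the aggregation method and the metric for each outcome, including whether it is a change from baseline. That file is not shown, and change scores are a plausible reading.
- *Inflation is worse because care aides are the test unit.* Inclusion and exclusion criteria sets its minimum response count so that outcomes can be aggregated by unit. The article gives no individual-level ICC.
- *A t test cannot serve three arms.* The hypotheses in the Discussion are pairwise, so pairwise tests are not an error in themselves.

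**Conclusion.** The concern holds in a limited form. The tests named for between-arm comparison of secondary outcomes, in their ordinary form, neither account for facility clustering nor carry the covariates promised for all analyses. The two sections must be reconciled.

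The size of the problem is conditional. For unit-level post-intervention values, a nominal two-sided 5% t test has a true size of about 13% if the outcome clusters like FI, 15% at the printed ICC, and 5-10% over assumed ICCs of 0.01-0.20. It is close to nominal for change scores with a constant facility effect, and nothing is added for outcomes measured once per facility. These figures assume alpha of 0.05, 3 units per facility and, for the top of the range, an ICC borrowed from FI.

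The inconsistency itself needs no assumed ICC. The primary analysis is already multilevel and is untouched, so this is a should-fix point.

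**What to change.** In Secondary analyses, replace the listed tests as the basis for between-arm inference on outcomes measured at unit level or below. Either of these would do:

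1. **Mixed models.** Fit linear or generalised linear mixed models with a facility random effect and, where a unit is measured repeatedly, a unit random effect. Adjust for region, owner-operator model and facility size. Use baseline either as a covariate or as one of the repeated outcomes, not both.
2. **Facility-level summaries.** Analyse one summary per facility with the same covariates. This also suits the facility-survey outcomes, for which unit random effects cannot be fitted.

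Keep the simple tests and the control charts as description. State for each secondary outcome the level of analysis and whether the comparison is of post-intervention values or of change, or point to where this is fixed.

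The cost is plan wording and a little programming, since a multilevel model is already planned for FI. Intervals for post-intervention comparisons widen by about √DE relative to a naive unit-level test: √1.02 = 1.01 at ICC 0.01, √1.40 = 1.18 at ICC 0.20, and √1.664 = 1.29 at the FI value. Use of baseline and covariates may recover part of that. No change to design, sample or data collection is needed.
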